## Materials and methods

### Trial design

This prospective, multicenter, randomized, open-label, parallel-group, practical clinical trial will enroll 3000 children from 30 centers in China. This trial is conducted in accordance with Declaration of Helsinki and Good Clinical Practice Guidelines, and approved by ethics committee institutional review board of each participating center. Subjects will be recruited after informed consent is obtained from the subjects and their guardian.

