### Power and sample size determination

This study hypothesis that S(+)-ketamine hydrochloride could significantly reduce pain scores and/or opioid consumption within 48 h after surgery compared with routine clinical practice. Due to the lack of reference for primary endpoint, the sample size will be evaluated under different effect size assumption. Assuming power is 80%, two-sided significant level 0.025, and the ratio of S(+)-ketamine hydrochloride group to conventional group is 2:1, the sample size under different effect sizes is shown in Table 1. As shown, about 687 patients will be powerful enough to detect an effect size of 0.25. The effect size d is defined as *d* = (μ1–μ2)/σ, and Cohen (1988) gave the interpretation of d=0.25 as 25% of σ and defines *d* = 0.2, 0.5, and 0.8 as small, medium, and large effect size. In our study, the used effect size of 0.25 is a relatively small effect size. By considering 4 types of surgery, we decide to include 3000 patients. Patients will stratify by age and surgical approach, and enrolled in a competitive enrollment way until the total number of research centers reached the expected sample size.

**Table 1 Tab1:** The sample sizes under different effect sizes

Control group (*N*)	S(+)-ketamine hydrochloride group (*N*)	Total subjects (*N*)	Effect sizes
58	116	174	0.500
130	260	390	0.333
229	458	687	0.250
357	714	1071	0.200
514	1028	1542	0.167
699	1398	2097	0.143
913	1826	2739	0.125
1155	2310	3465	0.111
1426	2852	4278	0.100

Sample size under different effect sizes assuming power is 80%, two-sided significant level of 0.025, and the ratio of S(+)-ketamine hydrochloride group to conventional group is 2:1

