### Intervention

In the control group, subjects will receive conventional therapy without S(+)-ketamine. There are no restrictions on drugs, doses, and incompatibility; the researchers can choose appropriate medication regimens based on clinical practice, but other NMDA receptor antagonists will not be allowed to use, such as dextromethorphan and amantadine.

In the trial group, S(+)-ketamine hydrochloride will be administrated for general anesthesia for anesthesia induction, maintenance, or postoperative analgesia. In principle, there are no specific restrictions on the dosage, way of administration, timing, and compatibility of S(+)-ketamine hydrochloride injection, but the recommended dosage is given. The recommended dose range for intravenous injection (1) for intravenous injection is as follows: (a) bolus intravenous injection before skin incision, the dose is 0.1–0.25 mg/kg; (b) bolus intravenous injection (dose 0.1–0.25 mg/kg) before skin incision and continuous intravenous infusion (dose of 0.1–0.25 mg/kg/h) during operation; and (c) continuous intravenous infusion after surgery with a dose of 0.02–0.1 mg/kg/h for 24–48 h and (2) for intramuscular injection as the dose is 2–4 mg/kg.

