### Participant timeline

After the subjects signed the informed consent, all subjects meeting the criteria will include in this study, stratified according to age and type of surgery. Clinical and demographic variables will be collected and reported including age, gender, blood tests, blood coagulation, urine routine, liver and kidney function, ECG, disease-related information (such as allergy history, present medical history, previous medical history, combined disease and concomitant medication), FLACC score, NRS score, AEs, and SAEs. After randomization, patients will be assessed on the screening period, preoperative, intraoperative, and at postoperative 10 min, 20 min, 30 min, 2 h, 4 h, 24 h, and 48 h. The participant flow is shown in Fig. 1. A time schedule for enrolment, interventions, and assessments is presented in Tables 2 and 3.

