### Statistical analysis

All statistical analyses will be performed using SAS 9.4 (SAS Institute Inc., USA). All data in this study will be analyzed according to the principle of ITT to reduce the deviation. The categorical data is expressed as numbers (%) and frequency and will be compared with Pearson chi-square or Fisher’s exact test. Continuous data will be expressed as mean ± standard deviations (SD) or median, minimum, maximum, interquartile range (IQR) and will be compared by Student’s *t* test and Wilcoxon rank-sum test.

For the primary endpoints, covariance analysis (ANCOVA) will be used to perform the between-group comparisons and the age and surgery types that are used as stratification factors in the randomization will be included as covariables. The FLACC scale score and NRS score will be analyzed separately, and then the standardized mean differences (SMD) will be combined by using the fixed effect meta-analysis model. To deal with the multiplicity problem caused by the two primary endpoints, the significance level will set be two-sided 0.025 by using the Bonferroni method. In subgroup analysis, according to age, type of surgery, intervention methods (such as drug administration method, dosage, type of other analgesics, presence or absence of nerve block, etc.) and possible combinations (combination plan of study drug and other drugs), subgroup analysis of the primary endpoints will be performed. For secondary endpoints, univariate analysis and multivariate analysis (Generalized Linear Mixed Model (GLMM)) will be used to perform the between-group comparisons. For safety analysis, the Pearson *χ*^2^ test or Fisher’s exact test will be used for comparison between groups. Effect sizes will be reported with 95% confidence intervals. All tests will be two-sided and the significance level is set as 0.025.

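### The primary ANCOVA names neither centre nor the screening pain score as a covariate, which may cost some precision, mainly for small effects and the surgery-type analyses, but does not affect validity

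*Protocol article*

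**What the plan says.** The Statistical analysis section of the Protocol article compares the groups on both primary endpoints by ANCOVA, and "the age and surgery types that are used as stratification factors in the randomization will be included as covariables". No other covariate is named. The same section gives a generalised linear mixed model to the secondary endpoints only. It analyses FLACC and NRS separately and then pools the standardised mean differences. For the two primary endpoints, "the significance level will set be two-sided 0.025 by using the Bonferroni method".

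Four other sections bear on the choice of covariates:

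- **Trial design:** the trial "will enroll 3000 children from 30 centers in China". Under Recruitment, enrolment is competitive.
- **Randomization and masking:** the strata are age and surgery type. Centre is not a stratum.
- **Intervention:** in the control arm "the researchers can choose appropriate medication regimens based on clinical practice", with other NMDA antagonists barred. In the trial arm dose, route, timing and drug combination are in principle unrestricted, with a recommended range.
- **Participant timeline:** the variables to be collected include "concomitant medication), FLACC score, NRS score, AEs, and SAEs". Tables 2 and 3 tick FLACC (age 7 and under) and NRS (age 8 to 17) at the screening visit.

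**The concern.** One primary endpoint is opioid consumption over 48 h and the other is a pain-score area over 48 h. Both depend on how children are anaesthetised and given analgesia, which the plan leaves open in both arms. Differences between centres in the outcome are therefore plausible. If they exist and the model has no centre term, they stay in the error variance.

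Since centre is not a stratum, the 2:1 split within a centre is also left to chance. At the average size of 3000/30 = 100 children, the treated share has an SD of about √((2/3)(1/3)/100) = 4.7 percentage points, taking allocation within a centre as simple random. That adds noise to an unadjusted comparison but no systematic error.

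The screening pain score raises the same question on a smaller scale: it is collected before treatment and the named model does not use it. At stake are interval width and power, chiefly where the trial has least to spare, in the comparisons by surgery type.

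**Working it through.** **Inputs from the article.** "Assuming power is 80%, two-sided significant level 0.025"; "the ratio of S(+)-ketamine hydrochloride group to conventional group is 2:1"; total N = 3000, hence 2000 : 1000; 30 centres; four surgery types.

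**Assumptions.** The article gives neither a centre ICC nor a correlation r between screening score and outcome. The ICC meant here is what remains after age and surgery type, and it is set at 0.01, 0.05, 0.10 and 0.20. Surgery types are taken as equal, 3000/4 = 750 each (500 : 250). The treatment effect is taken as the same in every centre.

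**1. The plan's own figure.** Control n = 1.5 × (z₀.₉₈₇₅ + z₀.₈₀)²/d² = 1.5 × (2.2414 + 0.8416)²/0.25² = 228.1, rounded up to 229. The total is 3 × 229 = 687, which agrees with the statement that "about 687 patients will be powerful enough to detect an effect size of 0.25". The other rows of Table 1 reproduce to within one control patient. The formula takes no credit for any covariate.

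**2. Power with no centre term.** In SD units, SE = √(1/n₁ + 1/n₂), and power = Φ(d/SE − 2.2414).

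- N = 3000: SE = √(1/2000 + 1/1000) = 0.0387. The detectable d at 80% power is 3.083 × 0.0387 = 0.119. Power is above 99.99% at d = 0.25, 80.4% at d = 0.12 and 63.3% at d = 0.10.
- N = 750: SE = √(1/500 + 1/250) = 0.0775. Power at d = 0.25 is Φ(3.228 − 2.241) = 83.8%.

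**3. With centre modelled.** The SE is multiplied by √(1 − ICC).

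| Assumed residual ICC | SE factor | Detectable d, N = 3000 | Power d = 0.10, N = 3000 | Power d = 0.12, N = 3000 | Power d = 0.25, N = 750 |
|---|---|---|---|---|---|
| 0 (no gain) | 1.000 | 0.119 | 63.3% | 80.4% | 83.8% |
| 0.01 | 0.995 | 0.119 | 63.8% | 80.9% | 84.2% |
| 0.05 | 0.975 | 0.116 | 65.8% | 82.6% | 85.8% |
| 0.10 | 0.949 | 0.113 | 68.4% | 84.7% | 87.7% |
| 0.20 | 0.894 | 0.107 | 74.1% | 88.9% | 91.4% |

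**4. Cost of estimating centre.** The table ignores this cost, so its gains are upper values. With 30 fixed centre effects the variance rises by 2998/2969 = 1.010 at N = 3000, so fixed effects pay only if the ICC exceeds about 0.01. Fitted within one surgery type of 750, the factor is 748/719 = 1.040. At ICC 0.05 the net variance is then 0.95 × 1.040 = 0.988, and most of the gain is gone. A random intercept loses less, and a model fitted to all surgery types together less again.

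**5. Validity.** A simulation of 30 centres with randomisation not stratified by centre (N = 3000, 1,500 trials per setting) gave these results at nominal 2.5%:

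| ICC | Type I error without / with centre | Power at d = 0.10 without / with centre |
|---|---|---|
| 0.05 | 2.0% / 1.9% | 63% / 66% |
| 0.10 | 2.8% / 3.3% | 64% / 69% |
| 0.20 | 1.9% / 2.4% | 62% / 71% |

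The Monte Carlo error of each type I figure is √(0.025 × 0.975/1500) = 0.4 points, so none departs clearly from nominal.

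**6. Screening score.** The share of variance removed is r²: 1% at r = 0.1 and 4% at r = 0.2.

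**The case against.** The strongest reply is that the stated model is valid and matches the design: it adjusts for the factors used in randomisation and drops none of them. The sample size assumes no covariate gain, so no planned power is lost. With 3000 children the planned effect of 0.25 is detected almost surely. The article does not say that age and surgery type are the only covariates, and an analysis plan that is not at hand may add others. All of this stands.

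It also stands that the size of any centre effect is conjecture. The article lets the researchers choose the regimen, so variation may lie between clinicians or patients within a centre, where a centre term does not help. Under Implementation, the investigators are to write an SOP to keep standards alike across centres.

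The reply does not remove the point about surgery types. The article raises the sample from 687 to 3000 by reference to the four types (4 × 687 = 2748) and plans subgroup analyses of the primary endpoints by type. At about 750 children, power is near 84% and not near 100%. The covariate set is stated for the confirmatory model, so this concerns a choice that was made and not a detail left out.

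**Conclusion.** The point holds as a moderate matter of efficiency. The named primary model leaves out centre, a plausible source of variance in this design, and a baseline score already collected. The gain from centre depends on an ICC that the article does not give: negligible at 0.01, and at 0.05 to 0.20 an SE lower by about 2.5% to 11%. In a surgery type of 750 that means power for d = 0.25 of at most about 86% to 91% in place of 83.8%. The equal split is also assumed, and competitive enrolment does not guarantee it.

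A reader might infer more, in four ways that the article does not support:

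- **That the primary result would be biased or the test invalid.** Randomisation protects both, and the simulation agrees.
- **That the trial forfeits hundreds of children.** The equivalent is 3000/(1 − ICC) − 3000, or 30, 158, 333 and 750 at the four assumed ICCs. It is measured against a better model and not against the planned power.
- **That the screening score would sharpen both primary endpoints.** The surgery is elective and the score is taken up to seven days beforehand, so it may vary little. Nothing in the article links it to opioid use.
- **That age adjusts for nothing in the separate FLACC and NRS models.** This would need a stratum cut at 7/8 years entered as a category, and the article does not give the age strata.

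**What to change.** Add to the primary analysis, before any unblinded analysis:

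1. A random intercept for centre in the models for both primary endpoints, beside treatment, age and surgery type.
2. The screening score as a covariate in the FLACC and NRS area models only: FLACC in the younger group, NRS in the older. The expected gain is small, about 1% to 4% of variance at r = 0.1 to 0.2.
3. The SD that standardises each mean difference before pooling. Dividing by the residual SD after centre adjustment would enlarge the effect by 1/√(1 − ICC). At ICC 0.10 that is 1/0.949 = 1.054, so d = 0.25 would read about 0.26 with no change in the treatment effect. The unadjusted pooled SD keeps the result on the scale of Table 1.

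The cost is a few sentences and a slightly more complex model. The screening scores are already scheduled, and centre is known for every child. If centre explains almost nothing, the loss from a random intercept is negligible; with 30 fixed effects it would be about 1% of variance at N = 3000.

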### Objectives

The primary objective of this study is to evaluate the analgesic effect of perioperative administration with S(+)-ketamine hydrochloride injection based on traditional anesthesia strategies on postoperative acute pain in children undergoing surgery. The secondary objectives of this study are (1) to explore the effect of perioperative administration of S(+)-ketamine hydrochloride injection on postoperative emergency delirium, anxiety and depression mood in children undergoing surgery; (2) to evaluate the safety of perioperative administration of S(+)-ketamine hydrochloride injection in children; and (3) to explore the optimal drug regimen of perioperative S(+)-ketamine hydrochloride injection for children, including the influence of administration route, dosage, timing, compatibility, and type of surgery on the end point of the study.

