### Randomization and masking

To ensure the comparability of groups, a stratified block randomization method with stratified factors for age and different surgical methods was adopted. An independent statistician generated the stratified permuted block randomization sequence by using SAS software (version 9.4, SAS Institute, USA). Centralized randomization was conducted by using the Interactive Voice Response service provided by Shang Hai Ashermed healthcare communications co., Ltd. Subjects meeting the criteria will be randomly assigned to the trial group or routine clinical practice group (control group) in a 2:1 ratio. The trial group will be administrated with S(+)-ketamine hydrochloride injection and the control group will receive conventional therapy without S(+)-ketamine hydrochloride injection. The most common usage in conventional therapy is propofol combined with an opioid.

The patients will be randomly allocated via an interactive response technology (IRT) system which is independent of the trial team. For each patient, nobody has any access to known the intervention that will be received during the screening stage. Block randomization will be done at the individual level with a randomization list generated by the IRT provider and will be stratified by age and different surgical types. The trial manager will inform the participant after notification of intervention allocation.

Since this is an open-label pragmatic trial, the investigators, the subjects and the sponsors who give intervention cannot be masked from intervention allocation. Notably, the investigator and pain score assessor is not the same one in this trial. The pain score assessor will not be informed of the grouping situation.

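### Subgroups defined by the regimen given (route, dose, other analgesics, nerve block) are not randomised comparisons: they can generate hypotheses but cannot support a causal best-usage conclusion

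*Protocol article*

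**What the plan says.** Randomisation and masking: children are "randomly assigned to the trial group or routine clinical practice group (control group) in a 2:1 ratio", stratified by age and surgery type. Nothing else about treatment is randomised. The same section says that "the investigators, the subjects and the sponsors who give intervention cannot be masked from intervention allocation"; only the pain score assessor is kept unaware of the group.

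Intervention: in the trial arm "S(+)-ketamine hydrochloride will be administrated for general anesthesia for anesthesia induction, maintenance, or postoperative analgesia", and in principle "there are no specific restrictions on the dosage, way of administration, timing, and compatibility of S(+)-ketamine hydrochloride injection", with recommended ranges only. In the control arm "the researchers can choose appropriate medication regimens based on clinical practice", except that other NMDA receptor antagonists are not allowed.

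Tables 2 and 3: randomisation is at the preoperative V1 visit. Analgesic dosage is recorded during surgery and at 24 h and 48 h.

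Statistical analysis: after age and type of surgery, the subgroup list continues with "intervention methods (such as drug administration method, dosage, type of other analgesics, presence or absence of nerve block, etc" and ends with "possible combinations (combination plan of study drug and other drugs), subgroup analysis of the primary endpoints will be performed". All of these stand in one sentence. Baseline factors are not separated from descriptions of treatment given.

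Objectives: the third secondary objective is "to explore the optimal drug regimen of perioperative S(+)-ketamine hydrochloride injection for children". Two other places go further. The end of the Introduction says that the trial should find the best way to use the drug. The end of the Discussion counts subgroup analysis among the means of lowering the risk of bias and producing high-quality evidence.

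**The concern.** A subgroup analysis keeps the protection of randomisation when the subgroup is fixed before allocation. Age and surgery type meet that condition. The regimen variables do not, for two reasons.

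- S(+)-ketamine route and dose have no counterpart in the control arm. A dose subgroup must be either a comparison of clinician-chosen regimens within the trial arm or a selected part of the trial arm against all controls. Neither is randomised.
- Other analgesics and nerve block occur in both arms, but a clinician who knows the allocation may choose them, and the choice may depend on the allocation. Children with a block in one arm may then differ from children with a block in the other.

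If children expected to have more pain receive a different regimen, that difference in prognosis shows up as a regimen effect. At stake is whatever the trial reports about dose, route, timing and compatibility. The main comparison is not at stake.

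**Working it through.** **The plan's own figure.** Power and sample size determination gives 687 children for d = 0.25 (80% power, two-sided 0.025, 2:1). With the normal approximation, controls = 1.5 × (2.2414 + 0.8416)² / 0.25² = 1.5 × 9.505 / 0.0625 = 228.1, rounded up to 229, and 3 × 229 = 687. The figure reproduces. So do the other rows of Table 1, apart from a gap of one control (129 against 130) at d = 0.333. No stated number is in dispute; 0.25 SD serves only as a yardstick.

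**Order of events.** Randomisation is at V1, before induction. S(+)-ketamine is given at induction, during maintenance or after surgery, and doses are recorded from surgery onward. Dose and route as given are therefore post-randomisation variables. For nerve block and co-analgesia the article does not say when the decision is made.

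**Illustration of size.** None of these inputs comes from the documents except the 2:1 ratio and the total of 3000 (2000 trial, 1000 control). Assume no true effect of drug or dose, an outcome with SD 1, and a normally distributed tendency to choose a regimen that has correlation r with the outcome.

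- Dose, split at its median within the trial arm: the mean of a standard normal above 0 is 0.798, so the spurious high-minus-low difference is 2 × 0.798 × r = 1.596 r.
- Nerve block, given to the top 30% of expected pain in the trial arm and the top 50% in control: the means above those cut-offs are 1.159 and 0.798, so the spurious trial-minus-control difference among children with a block is (1.159 − 0.798) × r = 0.361 r.

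A simulation of 2000 trials per row, using unadjusted t tests at two-sided 0.025, agrees with these formulas:

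| r | Dose: formula | Dose: simulated | False positives | Block: formula | Block: simulated | False positives |
|---|---|---|---|---|---|---|
| 0.01 | 0.016 | 0.016 | 2.9% | 0.004 | 0.001 | 3.6% |
| 0.04 | 0.064 | 0.064 | 21% | 0.014 | 0.015 | 3.0% |
| 0.09 | 0.144 | 0.144 | 83% | 0.032 | 0.035 | 4.5% |
| 0.25 | 0.399 | 0.399 | 100% | 0.090 | 0.091 | 25% |

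The dose bias reaches the planning effect of 0.25 SD at r = 0.25 / 1.596 = 0.157. Because the plan adjusts the primary endpoints for age and surgery type, r is best read as the correlation left within those strata.

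**Effect of a large sample.** A larger trial does not shrink this bias; it makes the bias more likely to be declared significant.

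**The case against.** *The objective is exploratory.* It is a secondary objective, introduced by the word explore, and no alpha or sample size is tied to regimen subgroups. This stands. A reader might infer that these analyses cannot serve the objective at all. The documents do not support that, because non-randomised contrasts can generate hypotheses. What they cannot carry is the stronger wording of the Introduction and Discussion.

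*The model already adjusts for surgery type.* The primary endpoints are compared by ANCOVA with age and surgery type, and the natural reading is that the subgroup analyses use the same model. This stands in part. A reader might build a crude example in which half the children have high-pain surgery (+1 SD) and blocks are used in 80% of high-pain and 20% of low-pain controls, against 40% and 20% in the trial arm. Among children without a block, the high-pain share is then 0.2/(0.2 + 0.8) = 0.20 in control and 0.6/(0.6 + 0.8) = 0.43 in the trial arm, a spurious 0.23 SD against S(+)-ketamine. That figure should not be used to say that the bias equals the planning effect. Its block rates are invented, and its confounder would disappear under adjustment if it coincided with surgery type. What survives is the part of expected pain that age and four broad types of surgery do not explain.

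*Blocks may be planned before randomisation.* This is possible. A reader might infer that every block is chosen after allocation, but the article does not say so. It also does not say that the intention is recorded beforehand, so the subgroup cannot be assumed to be a baseline one.

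*The analysis plan may add labels and adjustment.* It may, and their absence from a condensed article is no fault. The point rests on what the article states: treatment-given variables in one list with baseline factors, and subgroup analysis presented as a way of lowering bias.

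*Pragmatic trials leave regimens free.* Agreed. The point concerns how free choices are analysed, not that they are free.

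**Conclusion.** The concern holds in a limited form. Subgroups by S(+)-ketamine route and dose are not randomised comparisons. Those by other analgesics, nerve block and drug combination cannot be assumed to be, because the choice may be made with the allocation known. They can suggest hypotheses about regimen but cannot support a causal conclusion on best usage.

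The mechanism follows from the design as described. The size does not: it is unknown, and the illustrative ranges (near 0 to about 0.1 SD for nerve block, about 0.02 to 0.4 SD for dose) rest wholly on assumed correlations and block rates. Adjustment for age and surgery type would remove part of the bias, by an amount that the documents do not allow one to state.

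Subgroups by age and surgery type are sound, and so is the overall intention-to-treat comparison. The change is worth making because it decides what the trial may say about regimen, but it does not bear on the primary result.

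**What to change.** 1. Restrict treatment-by-subgroup (interaction) tests on the primary endpoints to variables fixed before randomisation: age, surgery type and centre. Include nerve block only if the plan to use one was recorded before allocation.
2. Move dose, route, other analgesics, nerve block as given and drug combinations to a separate analysis. Label it non-randomised and hypothesis-generating, and adjust it for pre-specified baseline confounders (age, weight, surgery type, centre).
3. Align the wording: state in the third secondary objective that regimen findings are non-randomised, soften the best-usage aim in the Introduction, and in the Discussion do not present these subgroups as a means of reducing bias.

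The cost is weaker claims about regimen and a little more analysis work; no treatment changes. Recording the intended block and regimen in the allocation system before randomisation would be cleaner in principle. However, with an estimated start in May 2021, a 12-month enrolment period and publication in July 2022, it would probably reach few or no children, so the fix does not depend on it.

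### The two primary endpoints are tested at two-sided 0.025 but reported with 95% intervals, so interval and decision can disagree; the 0.025 level is also applied to secondary and safety tests without a reason

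*Protocol article*

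**What the plan says.** All the relevant statements stand in one paragraph of the protocol article, under Statistical analysis.

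- The reason for adjusting: "To deal with the multiplicity problem caused by the two primary endpoints".
- The adjustment: "the significance level will set be two-sided 0.025 by using the Bonferroni method".
- The safety comparisons are formal tests: a Pearson chi-square "test or Fisher’s exact test will be used for comparison between groups".
- The interval level, with no separate rule for the primary endpoints: "Effect sizes will be reported with 95% confidence intervals".
- The closing rule for everything: "All tests will be two-sided and the significance level is set as 0.025".

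The section Power and sample size determination uses the same test level: "Assuming power is 80%, two-sided significant level 0.025". It also frames the hypothesis so that a reduction in pain scores, in opioid consumption, or in both would count. With either endpoint able to carry the claim, some multiplicity adjustment is needed. Nowhere does the article give a 97.5% interval or say that the 95% intervals are descriptive only.

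**The concern.** A two-sided test at level α and an interval at level 1 − α give the same answer. A 0.025 test pairs with a 97.5% interval; a 95% interval pairs with a 0.05 test. The plan fixes one level for the decision and another for the interval, so a confirmatory endpoint could be declared non-significant beside a published interval that excludes zero. A reader who goes by the interval would then be working without the Bonferroni correction.

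The second part is the reach of the 0.025 level. It exists because there are two primary endpoints. That reason does not carry over to the ten secondary endpoints under Clinical assessment, to the subgroup analyses, or to safety, which is a stated secondary objective. Applied there, it neither controls error across the set nor helps to detect harm.

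**Working it through.** **Inputs.** From Power and sample size determination: 80% power, two-sided 0.025, allocation 2:1, effect size d = 0.25 giving 687 patients, planned total 3000. From Statistical analysis: 0.025 per primary endpoint, 95% intervals, 0.025 for all tests. The split into 2000 and 1000 follows from 3000 at 2:1 and assumes no dropout.

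**The plan's own figures reproduce.** Bonferroni: 0.05 / 2 = 0.025. Control group size at 2:1 is (1 + 1/2)(z₁ + z₂)² / d², with z₁ = 2.2414 (two-sided 0.025) and z₂ = 0.8416 (80% power):

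1.5 × (3.083)² / 0.0625 = 228.1, so 229 controls, 458 treated, 687 in total, as stated. The other rows of Table 1 also agree to within rounding of the effect size. The sample size is thus consistent with the test level; only the interval level is not.

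**Width of the matching interval.** Estimate ± 2.2414 SE instead of ± 1.9600 SE; 2.2414 / 1.9600 = 1.144, or 14% wider.

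**Where test and interval disagree.** They disagree when 1.960 < |z| < 2.241, that is 0.025 < p < 0.05. With 1000 and 2000 patients the SE of d is √(1/1000 + 1/2000) = 0.0387, so the zone is:

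- lower edge 1.960 × 0.0387 = 0.076
- upper edge 2.241 × 0.0387 = 0.087

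Example: z = 2.1, p = 0.036, d = 0.081. The 95% interval is 0.005 to 0.157 and excludes zero; the 97.5% interval is −0.005 to 0.168 and includes it.

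**Error rate if intervals are read as tests** (no true effect, independent endpoints):

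- two 95% intervals: 1 − 0.95² = 9.75%
- two 97.5% intervals: 1 − 0.975² = 4.94%

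Without assuming independence, the bounds are 10% and 5%.

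**Chance of landing in the zone, per primary endpoint** (power at 0.05 minus power at 0.025):

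| True d | N | Power at 0.025 | Power at 0.05 | Chance of conflict |
|---|---|---|---|---|
| 0 | any | 2.5% | 5.0% | 2.5% |
| 0.25 | 3000 | 99.999% | above 99.999% | about 0.001% |
| 0.125 | 3000 | 83.8% | 89.8% | 6.0% |
| 0.10 | 3000 | 63.3% | 73.3% | 10.0% |
| 0.25 | 687 | 80.2% | 87.1% | 6.9% |

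The second row has noncentrality 0.25 / 0.0387 = 6.45, far above both critical values. The last row is for comparison only; the trial does not stop at 687.

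**The 0.025 level outside the primary endpoints.** With ten independent tests at 0.025, one per listed secondary endpoint, the chance of at least one false positive is 1 − 0.975¹⁰ = 22%. Several of these endpoints have multiple components or time points, so the number of tests may be larger. For safety, a difference that has 80% power at 0.05 has noncentrality 1.960 + 0.842 = 2.802. At 0.025 its power is Φ(2.802 − 2.241) = Φ(0.560), about 71%.

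**The case against.** The strongest reply is that nothing is wrong with the inference. The declared decision rule is the test at 0.025, its family-wise error is at most 5%, and a 95% interval labelled as such has its stated coverage. Nominal 95% intervals are a common descriptive convention. This stands. A reader might infer that the plan inflates its type I error or cancels its multiplicity control; the documents do not support that. The 9.8% arises only if the stated rule is set aside and the intervals are used as tests.

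A reader might also take the 6.9% conflict rate as applying at the planned effect. It needs 80% power at 0.025, which at d = 0.25 means 687 patients, while the trial enrols 3000. At that size and effect the conflict practically never occurs. It becomes material only for smaller effects. Those cannot be dismissed, because the article says that it has no reference for the primary endpoint and Table 1 goes down to d = 0.10.

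A further temptation is to call Bonferroni a mistake because Holm is more powerful. Bonferroni is valid, prespecified and consistent with the sample size. Holm's gain in establishing both endpoints (64% to 75%, independent) again assumes 80% power on each; at d = 0.25 with 3000 patients the chance exceeds 99.99% under either method.

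On safety, the article ties no decision to p < 0.025, and the 95% interval sentence follows directly on the safety tests. It could even be read as meant for them alone. Its wording is not so limited, however, and on that narrower reading the mismatch would still apply to safety tests at 0.025.

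**Conclusion.** The point holds as an inconsistency between reporting level and decision level on the two confirmatory endpoints, together with a significance level extended beyond its stated reason. Test level, Bonferroni split and sample size agree with one another and need no change. The practical size is modest: a zone of observed d from about 0.076 to 0.087, entered with probability 2.5% per endpoint under no effect, about 6% at d = 0.125, and virtually never at d = 0.25.

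These figures assume a normal approximation, a full 2000 versus 1000 and the SE of a simple two-group comparison. Covariate adjustment, dropout or the pooling of the two pain scales would shift the zone slightly. The mismatch itself depends on none of these.

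For secondary and safety tests, 0.025 is a stricter level per test but gives no family-wise control. In safety it costs about nine points of power for a difference that would have 80% at 0.05.

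**What to change.** Three wording changes in the Statistical analysis section:

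1. Report the two primary endpoints with 97.5% intervals. A 95% interval may be added if it is labelled descriptive and not used for the decision.
2. Limit the 0.025 level to the two primary endpoints.
3. Report secondary and safety comparisons as estimates with 95% intervals, without the 0.025 threshold.

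The cost is primary intervals about 14% wider. Sample size, data collection and the primary tests are unaffected, since Table 1 already uses 0.025. Holm over the two primary endpoints is an optional alternative with the same 5% family-wise error, but its matching intervals are less simple, and it is not needed to resolve this point.
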